## Subgroup analysis

We plan to explore treatment effects according to the following parameters: (1) CS secondary to acute myocardial infarction, (2) or postcardiotomy, (3) etomidate use, (4) vasopressor support, and (5) adrenal profiles (CIRCI and nonresponders to corticotropin stimulation test) [14, 18, 25].

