## Sample size and statistical analysis

Based on literature [14], the primary endpoint (catecholamine-free days at day 7) is estimated at 3 ± 3 days. The increase in this number of days reasonably expected in the corticosteroid group is + 1 day [11, 12, 19]. With a bilateral formulation, 190 patients will be needed in each group (total of 380 patients), with a statistical power of 90% and an α risk of 5% to conclude to the efficacy of the experimental group.

An intention-to-treat (ITT) and a per-protocol (PP) analysis will be performed. Following the ITT principle, all randomized patients receiving at least one dose of study medication will be included in the analysis with group allocation as randomized. The PP population will be composed of patients included in the study, without major deviations from the protocol, including erroneous inclusion of patients not meeting all selection criteria, modifications or non-compliance with the initial allocated treatment, and appearance of a formal indication for corticosteroid therapy during experimental period. The primary endpoint analysis will be performed on the ITT population. Additional analyses of the primary endpoint and all secondary endpoint analyses will be performed on both the ITT and PP populations in order to describe patients excluded from the PP population and assess the impact on the ITT analysis and the robustness of the results obtained.

Any missing or invalid data will be systematically checked and searched for in the medical records of the patient concerned. In addition to the analyses of complete cases without missing data for the primary endpoint, sensitivity analyses will be performed using several methods of replacing missing data, including the Last Observation Carry Forward (LOCF) method, the worst-case scenario assumption, and multiple imputation chain equation (MICE) techniques. There are no plans to replace subjects who left the study prematurely.

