No intermediate analysis is planned. STATA v14.1 (Stata Corp, College Station, TX, USA) and R 3.2.4 (R Foundation for Statistical Computing, Vienna, Austria) will be used for data analysis. The primary endpoint will be catecholamine-free days at day 7. The analysis of the primary endpoint will be carried out on the ITT population. Additional sensitivity analyses will be conducted on the PP population. Descriptive analyses will be performed. Normally distributed variables will be expressed as mean and standard deviations; non-normally distributed variables will be expressed as medians and inter quartile ranges. For categorical variables, number of patients in each category and corresponding percentages will be given. The effects of treatments on mortality rates will be compared using a logistic regression. Cumulative event curves (censored endpoints) will be estimated with Kaplan–Meier procedure, and Cox model will be used to compare treatments effects. Analysis of variance will be used to compare number of days alive and free of vasopressors, MV, and with a cardiovascular SOFA score < 3. The same analyses will be conducted for subgroups unless the numbers of patients are insufficient. In this case, statistical methods will be adapted according to sample sizes.

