## Discussion

The COCCA study is the first randomized controlled trial to investigate low dose of corticosteroid therapy in adult patients with CS. This trial investigates the hemodynamic effects of hydrocortisone and fludrocortisone and replicates as much as possible the intervention of APROCCHSS trial in septic shock patients [12].

Corticosteroids have been considered in the management of several acute illnesses [18, 26]. During septic shock, it is now clear that the use of low-dose corticosteroids enhance shock reversal [7–9], with acceptable side effects as hyperglycemia and hypernatremia, and potential survival benefits [9]. These results were recently confirmed by APROCCHSS and ADRENAL trials [11, 12]. Corticosteroids have cardiovascular effects during shock, with an increase in mean arterial pressure, and systemic vascular resistance [27, 28]. Corticosteroids can improve vasopressor sensibility [20], especially in case of adrenal dysfunction [29, 30], through an increase in α adrenergic receptor gene expression [31] and endothelial glucocorticoid receptors [32]. Additionally, corticosteroids probably improve cardiac function [33–38], especially in patients with circulatory shock with long-term catecholamine treatment [39, 40]. Given the many similarities between CS and septic shock with a SIRS-like pathophysiology, we can expect a hemodynamic effect of low-dose corticosteroids in CS similar to that in septic shock. Moreover, it seems interesting to identify subgroups of patients more likely to benefit from corticosteroids [19] and those at high risk of harm [41]. This study will attempt to provide robust answers about the usefulness of corticosteroid replacement therapy in adult with CS [42].

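### Subgroups are to be analysed by repeating the main comparisons, with no treatment-by-subgroup test stated, although the question is who benefits or is harmed

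*Protocol article*

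**What the plan says.** The Subgroup analysis section opens with "We plan to explore treatment effects according to the following parameters" and lists five: infarct-related shock, shock after cardiac surgery, exposure to etomidate, being on a vasopressor, and adrenal status. The last covers two definitions, "adrenal profiles (CIRCI and nonresponders to corticotropin stimulation test"), so there are six factors if these are counted separately.

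The method is in Sample size and statistical analysis. That section names logistic regression for mortality, Kaplan–Meier and Cox for time-to-event outcomes, and analysis of variance for day counts. It then says "The same analyses will be conducted for subgroups unless the numbers of patients are insufficient", and continues: "In this case, statistical methods will be adapted according to sample sizes". No interaction or heterogeneity test appears anywhere in the article.

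The purpose is in the Discussion: "it seems interesting to identify subgroups of patients more likely to benefit from corticosteroids", and also those at high risk of harm. Risk of bias and study limitations then relies on the etomidate and phenotype subgroups to answer two limitations it acknowledges, etomidate exposure and a broad case mix.

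**The concern.** Whether the drug works better in one kind of patient than in another is a question about a difference between two treatment effects. A treatment test run inside each stratum asks something else: whether the effect in that stratum differs from zero. Two strata with the same true effect can easily fall on opposite sides of 5%, above all when one is small.

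At stake is how the subgroup results are read. A result that is significant in patients with adrenal insufficiency and not in the rest, or the reverse for etomidate, invites a conclusion about whom to treat that the data may not support. The primary analysis is not affected.

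**Working it through.** **Inputs.** Sample size and statistical analysis gives a mean of 3 days with SD 3 for the primary endpoint, an assumed gain of 1 day with steroids, a two-sided 5% level, 90% power and 190 per group. Subgroup shares are not given, so they are varied here as an assumption. Like the protocol's own calculation, this treats the endpoint as approximately normal with SD 3.

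**Step 1: reproduce the protocol's figure.** n per arm = 2 × SD² × (1.960 + 1.282)² / δ² = 2 × 9 × 10.51 / 1 = 189.1, rounded up to 190. This matches. Power at 190 per arm is 90%.

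**Step 2: power inside a stratum, true effect +1 day in everyone.** With n per arm in the stratum, SE = 3 × √(2/n) and power = Φ(1/SE − 1.96).

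- Half the patients, n = 95: SE = 0.435, power = Φ(2.297 − 1.96) = 0.632.
- 30%, n = 57: SE = 0.562, power = Φ(1.779 − 1.96) = 0.428.
- 70%, n = 133: SE = 0.368, power = Φ(2.718 − 1.96) = 0.776.

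**Step 3: chance that exactly one of two complementary strata is significant.** The strata share no patients, so with powers p₁ and p₂ the chance is p₁(1 − p₂) + p₂(1 − p₁).

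| Split | Power, smaller stratum | Power, larger stratum | Exactly one significant |
|---|---|---|---|
| 50/50 | 63% | 63% | 2 × 0.632 × 0.368 = 47% |
| 30/70 | 43% | 78% | 0.428 × 0.224 + 0.776 × 0.572 = 54% |
| 20/80 | 31% | 83% | 0.306 × 0.172 + 0.828 × 0.694 = 63% |

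The effect is the same in both strata in every row, so each such contrast is spurious.

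**Step 4: the interaction test in the same situation.** It has its nominal 5% error per factor whatever the split. In 5,000 simulated trials per scenario the observed rate was 4.6% to 5.3%.

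**Step 5: no effect anywhere.** Exactly one stratum is significant with chance 2 × 0.05 × 0.95 = 9.5% per factor.

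**Step 6: what the interaction test can detect.** SE of the difference in effects = √(18/n₁ + 18/n₂), with n per arm in each stratum. At 50/50 this is √(18/95 + 18/95) = 0.616. Power for a 1-day difference in effect is Φ(1/0.616 − 1.96) = 37%. The difference detectable with 90% power is 0.616 × 3.242 = 2.0 days. At 20/80 the SE is 0.769, and the figures are 26% and 2.5 days.

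**The case against.** The strongest reply is that the article is a condensed protocol and no analysis plan is shown. The subgroup sentence names model families, all of which can carry an interaction term, and details of that kind often sit in the analysis plan. This stands in part. A reader might infer that no interaction test will be done; the article supports only that none is stated. It does not dispose of the point, because the article does give a method. A proviso about too few patients fits separate analyses of each subgroup most naturally, since an interaction model would use the whole trial.

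A second reply is that the subgroups are pre-defined and exploratory, that the formal Objective has no subgroup aim, and that nowhere is it said that claims will rest on within-stratum p-values. This is also fair: misreading is a risk, not a documented intention. But the Discussion and the limitations section give the subgroups a comparative job, and calling them exploratory does not make separate tests a comparison.

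Third, the clause on adapting methods could be read as a licence to choose methods after seeing results. The text does not support that. Adaptation is tied to sample size, not to the observed effect, and Randomization, comparator, and blinding keeps the analysts blinded. Using other methods for sparse strata is ordinary practice.

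Finally, a reader might multiply up the per-factor figures and conclude that nearly every trial would show at least one spurious contrast. Simulation of six independent factors with a uniform effect gives 83% to 92%, but this rests on assumed shares and on independence. The Cortisol assays section makes every nonresponder also a CIRCI patient, so those two factors are nested. No across-factor figure is relied on here.

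**Conclusion.** The concern holds as a mismatch between stated method and stated question. For each factor, if the true effect is a uniform +1 day, reading separate subgroup p-values gives a spurious contrast 47% of the time at a 50/50 split and 54% at 30/70, against 5% for an interaction test. If there is no effect, the figure falls to about 9.5%. The size of the problem therefore depends on the treatment working about as well as the protocol expects.

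The figures rest on the protocol's +1 day, SD 3 and 190 per arm, on approximate normality, and on assumed subgroup shares. The adrenal strata may be smaller than the total suggests, since Study interventions has the corticotropin test done only where feasible.

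**What to change.** For each pre-defined baseline factor, fit the same model as in the main analysis, in all patients (for adrenal status, all with a test result), with a treatment-by-factor interaction. Report the interaction estimate with its 95% CI and p-value, and the treatment effect in each stratum with its 95% CI. State that subgroup claims are exploratory and rest on the interaction, not on within-stratum p-values. The provision for sparse strata may stay.

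The cost is wording only. Etiology, etomidate and vasopressor use are already baseline data, and the corticotropin test precedes study drug. The downside is low power: about 37% for a 1-day difference in effect at 50/50, so fewer subgroup claims can be made. Interaction tests do not remove multiplicity either. Five at 5% would, if independent, give at least one false positive with chance 1 − 0.95⁵ = 23%, a further reason to label the results exploratory.

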## Adverse event reporting

During hospitalization, patients are closely monitored for adverse events (AE) and serious adverse events (SAEs). Expected AEs are those that are anticipated in the population under study, regardless of participation in research. Expected SAEs in this study include the following: (1) severe infection (life-threatening, leading to death or septic shock); (2) refractory shock (defined as the need for MCS); (3) vascular disorders: stroke, myocardial infarction, peripheral arterial ischemia; (4) hypokalemia (< 3 mmol/L) and its consequences, if the event occurs between day 1 and day 8; (5) hypersensitivity reaction (including anaphylactic reaction); and (6) death from any cause. Any adverse event that meets a protocol-defined criterion as a SAE will be reported electronically to the data coordinating center without delay (within 24 h of site awareness) on SAE form. Moreover, suspected unexpected serious adverse reactions (SUSARs) will be registered. At any time after completion of the study, if the principal investigator or appropriate co-investigator becomes aware of an SAE, the principal investigator or appropriate co-investigator will report the event to the designated Pharmacovigilance Group. The intensity of adverse events will assess by the investigator according to the CTC-AE V4.0 classification. Safety analyses, as part of the endpoints, will be based on the safety set, consisting of the pre-defined SAEs, and will comprise standard descriptive methods.

## Study organization

The financial support and study promotion will be performed by *CMC Ambroise Paré*. An independent Data and Safety Monitoring Board (DSMB), that is not involved in the design and conduct of the trial, and has no affiliation with the sponsor, looks over the ethics in accordance with the Declaration of Helsinki, monitors patient safety, and reviews safety issues as the study progresses. SAEs and unexpected related or possibly related serious events are reported blindly to the DSMB. The sponsor has a liability insurance which is in accordance with national legislation, guaranteeing its own liability as well as that of the investigators. In accordance with applicable regulations and GCP, a study monitor is periodically controlling study procedures. A trial steering committee (TSC) will monitor the overall conduct of the trial. The TSC will make recommendations regarding all trial-related decisions including those based on recommendations from the DSMB.

## Protocol amendments

Important protocol modification (i.e., inclusion and exclusion criteria, outcome, analyses) will be informed to the Independent Ethics committee (*Comité de Protection des Personnes CPP— Ile-de-France IV*).

## Dissemination of research results

After completion of the study, its findings will be published in some international peer-reviewed journals and presented at national/international scientific conferences. Both positive and negative results will be published. A summary of the results will be made available to the study patients if requested. Concerning authorship, all researchers and other colleagues who participated in this study will be co-authors or collaborators of the study based on their individual contributions. All authors who fulfill the authorship criteria will be included in future publications. There is no intended use of professional medical writers. The full protocol, participant-level dataset, and statistical code will be available from the corresponding author on reasonable request.

## Discussion

The COCCA study is the first randomized controlled trial to investigate low dose of corticosteroid therapy in adult patients with CS. This trial investigates the hemodynamic effects of hydrocortisone and fludrocortisone and replicates as much as possible the intervention of APROCCHSS trial in septic shock patients [12].

Corticosteroids have been considered in the management of several acute illnesses [18, 26]. During septic shock, it is now clear that the use of low-dose corticosteroids enhance shock reversal [7–9], with acceptable side effects as hyperglycemia and hypernatremia, and potential survival benefits [9]. These results were recently confirmed by APROCCHSS and ADRENAL trials [11, 12]. Corticosteroids have cardiovascular effects during shock, with an increase in mean arterial pressure, and systemic vascular resistance [27, 28]. Corticosteroids can improve vasopressor sensibility [20], especially in case of adrenal dysfunction [29, 30], through an increase in α adrenergic receptor gene expression [31] and endothelial glucocorticoid receptors [32]. Additionally, corticosteroids probably improve cardiac function [33–38], especially in patients with circulatory shock with long-term catecholamine treatment [39, 40]. Given the many similarities between CS and septic shock with a SIRS-like pathophysiology, we can expect a hemodynamic effect of low-dose corticosteroids in CS similar to that in septic shock. Moreover, it seems interesting to identify subgroups of patients more likely to benefit from corticosteroids [19] and those at high risk of harm [41]. This study will attempt to provide robust answers about the usefulness of corticosteroid replacement therapy in adult with CS [42].

## Risk of bias and study limitations

The risks of bias of the COCCA study were minimized by a robust randomization (computer-generated and stratified by center) and a strong double-blind (with double placebo) design. We have chosen as comparator placebo in order to control the placebo effect and to minimize the potential bias resulting from differences in management, especially catecholamine weaning because of the nature of the primary endpoint (catecholamine-free days at day-7). Concerning our experimental arm, we have selected a corticosteroid regimen consisting of fludrocortisone plus hydrocortisone, because the only two RCTs showing a benefit on mortality used this combination in septic shock [12, 19]. Moreover, hydrocortisone was administrated as intermittent intravenous bolus and without taper off in these studies, as in ours. Meta-analyses have demonstrated that the administration method of hydrocortisone (intermittent bolus vs. continuous infusion) did not seem to influence the mortality, in contrast to the use of taper off [9].

The COCCA trial potentially includes some limitations. Firstly, the primary endpoint, catecholamine-free days at day 7, was chosen in part because an all-cause mortality endpoint would not have been realistic. Indeed, APROCCHSS and ADRENAL studies initially planned to analyze 1280 and 3800 patients, respectively, to detect a small difference in mortality. Second, we will exclude patients already undergoing MCS at time of inclusion, in whom the potential benefit of substitutive corticosteroid therapy is possibly high. Thirdly, exposure to etomidate in some patients could be problematic. Indeed, it is an adrenal suppressant drug, but it is also a widely used hypnotic agent for urgent intubation in CS. We have planned a subgroup analysis taking into account etomidate use. Last, the spectrum of patients with CS included is wide. Therefore, the most specific phenotypes of CS (acute myocardial infarction, postcardiotomy, need of vasopressor support) will be assessed by subgroup analyses.

In conclusion, the COCCA trial should help assess whether low dose corticosteroids are beneficial in adult patients with CS. This pragmatic study is the first large RCT focusing on substitutive corticosteroid therapy in CS.

## Trial status

This is version 9.0 of the protocol, dated 22 February 2021. The first patient was randomized on April 19, 2019. Recruitment is predicted to continue until April 2022. At the time of submission, participant recruitment is still ongoing.

## Data Availability

Dataset of this study will be available through the corresponding author if there is a reasonable request.

## Abbreviations

CIRCI: Critical illness-related corticosteroid insufficiency
HPA: Hypothalamo-pituitary-adrenal
ACTH: Adrenocorticotropic hormone
COCCA trial: COrticosteroid in Cardiogenic shoCk in Adult patient trial
ICU: Intensive care unit
*T*_max_: Maximal post stimulation cortisolemia concentration
Δ_max_: Maximal cortisol response
*T*_0_: Baseline cortisolemia
MAP: Mean arterial pressure
eCRF: Electronic case report forms
GCP: Compliant to good clinical practice
SAPS: Simplified Acute Physiology Score
SOFA score: Sequential organ failure score
RAS: Renin angiotensin system
LVEF: Left ventricular ejection fraction
S-mit: Systolic velocity at the mitral annulus
LV-GLS: Left ventricular global longitudinal strain
VTI: Velocity-time integral
LVOT: Left ventricular outflow tract
E: Early diastolic wave velocities at the mitral valve
A: Late diastolic wave velocities at the mitral valve
e’: Tissue Doppler early diastolic wave velocity at the lateral mitral valve annulus
S-tric: Systolic right ventricular function by tissue Doppler peak systolic wave at the lateral tricuspid annulus
TAPSE: Tricuspid annular plane systolic excursion
sPAP: Systolic pulmonary arterial pressure
MCS: Mechanical circulatory support
MV: Mechanical ventilation
ITT: Intention-to-treat
PP: Per-protocol
AE: Adverse events
SAE: Serious adverse events
SUSAR: Suspected unexpected serious adverse reactions
DSMB: Data and safety monitoring board
TSC: Trial steering committee
RCT: Randomized controlled trial
